## Abstract

**Background:**

Sleep disturbances are common non-motor symptoms in Parkinson's disease (PD), significantly diminishing patients' quality of life. Management typically involves sleep hygiene education, psychotherapy, pharmacological and non-pharmacological interventions. This study aims to explore the safety and effectiveness of repeated lower extremity hot water bathing (REHAB) as a potential treatment for sleep disorders in this patient population.

**Discussion:**

This novel randomized controlled trial will assess the safety and potential therapeutic benefits of REHAB for sleep disorders in elderly patients with advanced PD. The findings will inform design considerations for future phase III studies and may introduce a new rehabilitation strategy for managing sleep disturbances in this population.

**Trial registration:**

http://www.chictr.org.cn/, identifier: ChiCTR2400092087.

## Introduction

1

Parkinson's disease (PD) is a prevalent neurodegenerative disease marked by both motor and non-motor symptoms (1), with sleep disturbances affecting up to 98% of patients (2). The manifestations of PD sleep disturbances include sleep fragmentation, insomnia, rapid eye movement sleep behavior disorder (RBD), restless legs syndrome (RLS), and excessive daytime sleepiness (EDS). Such symptoms exacerbate motor dysfunction and reduce quality of life, particularly in advanced stages (3).

The management of sleep disorders in patients with PD often requires a collaborative and multifaceted approach, typically beginning with sleep hygiene education and effective non-pharmacological treatments. Consequently, non-pharmacological interventions, such as psychotherapy and physical therapies, are increasingly recommended as first-line treatments (4). Physical therapies, including exercise (5, 6), light therapy (7), transcranial magnetic stimulation (TMS) (8), and deep brain stimulation (DBS) (9), have demonstrated benefits for sleep quality in PD patients. However, their widespread use is limited by factors such as impaired mobility, the need for specialized equipment and trained professionals, and economic considerations.

The mechanisms of sleep disorders in PD are complex, involving neuronal degeneration and the accumulation of α-synuclein and tau proteins in brain regions critical for sleep regulation (10). Heat therapy has been proposed as a potential therapeutic approach by promoting the delivery of molecular mediators within extracellular vesicles, which help maintain balanced neurotransmission (11). Pre-clinical studies have shown that exposure to high temperatures can elevate circulating levels of dopamine and glutamate (12), potentially modulating dopaminergic transmission and receptor sensitivity while increasing striatal activity. In addition, heat therapy may upregulate heat shock proteins (HSPs), which play a protective role against α-synuclein aggregation in PD. Given their role in protein homeostasis, HSP expression has been proposed as a therapeutic target for neurodegenerative diseases (13).

Another area of focus is inflammation, as early stages of PD have been linked to gastrointestinal inflammation that may spread to the central nervous system (CNS) via the vagus nerve (14). Heat therapy has been shown to modulate inflammatory pathways, reduce chronic low-grade inflammation, induce anti-apoptotic and antioxidative effects, and enhance mitochondrial respiratory capacity. Collectively, these effects may slow neurodegenerative progression (15). Evidence suggests that heat therapy, through methods like hot water bathing or sauna use, may serve as an effective alternative to aerobic exercise for individuals with mobility impairments, offering potential benefits for the aging brain (16, 17). Regular heat therapy has been associated with a reduced risk of developing neurodegenerative conditions (18).

Thermoregulatory mechanisms play a key role in sleep, because warming is directly linked to sleep initiation. Elevating skin temperature can stimulate warm-sensitive neurons in the pre-optic area and anterior hypothalamus, increasing their firing rate and promoting sleep onset (19). Early studies have demonstrated that manipulating ambient temperature enhances sleep depth in mice (20). In both humans and other mammals, direct skin warming has been shown to shorten sleep latency, increase slow-wave-sleep (SWS), enhance Non-Rapid Eye Movement sleep (NREM) consolidation, and decrease Rapid Eye Movement sleep (REM) (21). In elderly individuals with insomnia, warming distal skin temperature has been shown to enhance slow-wave sleep (22). Thermal therapy applied to the extremities has also been explored as a complementary treatment to improve sleep quality in patients with chronic heart failure (23). Heat therapy has demonstrated potential in alleviating sleep disturbances following traumatic brain injury (24), promoting relaxation, reducing pain perception, and discomfort during sleep in cancer patients (25), decreasing symptoms of restless leg syndrome during pregnancy (26, 27), and improving sleep quality in chronic heart failure patients (23). Notably, the 2019 Global Sauna Cross-sectional Survey reported benefits of sauna use for health, particularly in terms of mental health and sleep, with relatively few side effects (18).

The current trial aims to provide evidence regarding the safety and efficacy of heat therapy in elderly patients with advanced PD with sleep disorders. Hot bathing has been found to be safe and effective in young, healthy individuals, as well as in obese populations (28). However, there are occasional reports of hot bathing causing transient symptomatic hypotension (29) in some individuals. Patients with PD often experience autonomic nervous system dysfunction, which increases the risk of neurogenic orthostatic hypotension (30).

Therefore, the objective of this trial is to first assess the safety and then evaluate the clinical efficacy of repeated lower extremity hot water bathing (REHAB) on sleep in patients with PD. REHAB is a structured, multidisciplinary rehabilitation program that involves daily immersion of the lower extremities in warm water. In this study, participants in the intervention group will immerse their legs up to around mid-calf in 41 °C water for 30 min per session using a thermostatic footbath device (Changhong, model CDN-ZY8808C; dimensions: 44 × 41.5 × 36.5 cm; compliant with Chinese executive standards GB4706.1-2005 and GB4706.10-2008). The results of this study will provide valuable evidence for a home-based treatment for PD patients and their families.

## Methods

2

### Study design

2.1

This is a single-center, prospective, randomized controlled trial designed to enroll elderly patients with advanced PD. All participants will be informed of the clinical research and the requirements for giving informed consent. The research plan and informed consent will be approved by the regional ethics committee; the trial is registered at www.chictr.org.cn (Registration number: ChiCTR2400092087).

Forty PD patients will be randomly assigned in a 1:1 ratio to the REHAB group or the control group. The control group will receive daily medication and rehabilitation therapy as recommended by the International Movement Disorders Society (31). The intervention group will receive REHAB in addition to guideline-based usual care. An independent physician will monitor the participants' health and safety via WeChat video calls.

### Inclusion and exclusion criteria

2.2

Participants will be recruited from both outpatient and inpatient centers at Beijing Luhe Hospital, Capital Medical University. The inclusion criteria are as follows: (1) diagnosis of PD according to the MDS clinical criteria; (2) 2.5 ≤ Hoehn-Yahr ≤ 4.0; (3) age between 60 and 80 years old; (4) PDSS score < 90; (5) stable condition and levodopa equivalent daily dose for ≥30 days; (6) obtained written informed consent from the participants or their legally authorized representative.

Exclusion criteria include patients diagnosed with mental illness (bipolar disorder, mania, schizophrenia etc.), substance abuse, uncontrolled cardiovascular disease, or other conditions such as local skin rupture, soft tissue injury, fracture, infection, and peripheral neuropathy in both lower extremities, that might impede their ability to participate in REHAB.

### Randomization and blinding

2.3

This trial employs a randomized controlled, open-label, outcome assessor-blinded design (32).

Eligible participants will be allocated via a centralized randomization system. An independent statistician, not involved in participant recruitment, intervention delivery, or outcome assessment, will generate the random allocation sequence using the PROC PLAN procedure in SAS 9.4 software (SAS Institute Inc., Cary, NC, USA). A block randomization method will be used to ensure balanced group sizes throughout the recruitment period. The generated sequence will be securely stored within an independent central randomization system. Upon completion of screening and provision of informed consent, the study coordinator will access this central system to obtain the participant's unique group assignment (REHAB group or control group).

### Interventions

2.4

#### Control group

2.4.1

Patients in the control group will continue their usual care, which includes a stable dose of medication and daily exercise for the management of PD, as per the recommendations of the International Parkinson and Movement Disorder Society (33, 34).

#### Intervention group (REHAB group)

2.4.2

In addition to continuing their usual stable dose of medication and daily exercise, participants in the REHAB group will perform REHAB using a thermostatic footbath device (Changhong, CDN-ZY8808C, executive standard GB4706. 1-2005 GB4706. 10-2008. dimensions: 44 × 41.5 × 36.5 cm). Initially, the principal investigator will demonstrate the correct use of the footbath device to the patients. Participants will then immerse their lower extremities in 41 °C water for 30 min per session (24). This will be performed once daily, for 5–7 days per week, over a total period of 4 weeks (35). The recommended time for REHAB is 1 to 2 h prior to bedtime (Figure 1).

**Figure 1 F1:**
[figure not shown]
Flow chart of the repeated lower extremities hot water bathing study.

#### Data collection and monitoring for all participants

2.4.3

Patients in both groups must maintain a daily log tracking their blood pressure, heart rate, and body temperature. For the intervention group, these measurements will be taken immediately before and after each REHAB session. All logs, which will also note any discomfort experienced, will be submitted to the researchers via WeChat. To ensure compliance with the study protocol, a study assistant will conduct daily check-ins with all participants over WeChat video.

Our study prioritizes the tolerability and safety of REHAB for patients. Exposure to 41 °C hot water bathing is generally considered safe, even during pregnancy (27). However, PD-associated autonomic dysfunction (e.g., hyperhidrosis, anhidrosis, orthostatic hypotension) may cause discomfort. To mitigate risks, participants will be advised to drink plenty of water, wipe away sweat with a towel, and lie flat under a thin blanket for 15 min after soaking to allow blood pressure to return to normal and reduce the potential risk of syncope-related falls. If participants experience nausea, dizziness, or significant discomfort, the treatment will be discontinued.

**Sociodemographic characteristics**			
Gender (M/F)	X		
Age (*y*)	X		
Duration of PD (*y*)	X		
Hoehn–Yahr (stage)	X		
UPDRSIII (“on” stage, score)	X	X	X
PDSS (score)	X	X	X
**PSG (Compumedics, Australia Germany, Type Grael)**			
Total sleep time (TST) (s)	X	X	
Sleep efficiency (SE) (%)	X	X	
Sleep latency (SL) (s)	X	X	
Arousal index (AI) (*n*)	X	X	
Non-rapid eye movement sleep stages N1 (%)	X	X	
Non-rapid eye movement sleep stages N2 (%)	X	X	
Non-rapid eye movement sleep stages N3 (%)	X	X	
Adverse events (AEs; *n*)		X^a^	X^b^
Adherence rate (%)		X^c^	X^d^

^a^Intervention monitoring data (V0 to Visit 1, Weeks 1–4): summarized from daily recordings. Adverse events: total count during the entire intervention period;

^b^Data from V1 to Visit 2 (Weeks 5–6);

^c^Adherence rate from V0 to V1: calculated as (number of days the participant followed the investigator's instructions/total expected days) × 100%;

^d^Adherence rate from V1 to V2: calculated similarly.

**Figure 2 F2:**
[figure not shown]
Diagram of lower leg and foot hot water bathing.

### Outcomes

2.6

#### Primary outcomes

2.6.1

The primary objective of this study is to assess the safety of REHAB. Adverse events will be closely monitored including: 1) symptomatic hypotension, which has been reported in association with hot bathing and may be exacerbated in PD due to autonomic dysfunction (29, 30); 2) Scald or intolerance as sensory impairments in PD may also lead to altered sensitivity to water temperature, increasing the risk of burns are intolerance to REHAB (37); 3) Systemic symptoms, such as headache, dizziness, palpitations, sweating, etc.; 4) Signs of tissue or neurovascular injury due to REHAB, including erythema, skin damage, tenderness upon palpation, and local edema.

All adverse events will be carefully assessed by trained research personnel blinded to randomization. Blood pressure, heart rate, and core body temperature we will be recorded before and after each session to further evaluate safety, and these physiological parameters will be incorporated into the safety analysis.

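### The primary safety outcome lists sweating and erythema without grading and summarises adverse events as one total, while syncope and falls, which the protocol guards against, are not named or specifically asked about

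*Protocol article*

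**What the plan says.** Section 2.6.1 makes safety the primary aim: "The primary objective of this study is to assess the safety of REHAB". It then gives four numbered groups of events. The first is symptomatic hypotension ("Adverse events will be closely monitored including: 1) symptomatic hypotension"), and the second is scald or intolerance. The third is "Systemic symptoms, such as headache, dizziness, palpitations, sweating, etc", and the fourth is "Signs of tissue or neurovascular injury due to REHAB, including erythema, skin damage, tenderness upon palpation, and local edema". Neither sweating nor erythema carries a threshold of severity, duration or expectedness. Blood pressure, heart rate and body temperature are added to the safety analysis.

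Section 2.4.3 tells REHAB participants to "drink plenty of water, wipe away sweat with a towel, and lie flat under a thin blanket for 15 min after soaking". The stated purpose of lying down is to let blood pressure recover and to "reduce the potential risk of syncope-related falls". The same section names excessive sweating as a form of PD-related autonomic dysfunction. Participants in both arms log blood pressure, heart rate, temperature and any discomfort, and a study assistant makes a daily video check-in, whose stated purpose is compliance. Section 2.1 adds an independent physician who follows health and safety by video call.

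Table 1, note a, describes the Visit 1 entry for weeks 1 to 4: "Adverse events: total count during the entire intervention period". Note b covers weeks 5 and 6. The safety concerns in the abstract are orthostatic hypotension, scalds or intolerance, and tissue damage. Syncope and falls are not among them.

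**The concern.** The adverse-event list is the primary outcome, so what it names and how it is summed decide what the trial can say about safety. Two features work against it.

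First, one response, sweating, is treated in section 2.4.3 as something to be wiped away after a bath and in section 2.6.1 as a primary adverse event. No rule separates the two cases. Erythema of skin just taken from hot water raises the same question: passing redness and redness that signals injury fall under one word. In a total count, each such entry weighs as much as a scald or a faint, and one participant can contribute an entry at every session.

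Second, the harm for which section 2.4.3 takes an explicit precaution is not named as an outcome. A fall at night or the next morning is not plainly a discomfort, and nothing in the article says that participants are asked about falls or loss of consciousness.

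Section 2.7 says the findings will inform safety and feasibility assessments and the planning of Phase III trials. For that use, serious events must be visible separately from expected reactions. A fall that was not asked about at the time cannot be recovered reliably afterwards.

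**Working it through.** The article states no adverse-event rate, safety threshold or power for safety, so there is no figure to reproduce. The check is mainly of the text, with an illustration of scale.

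**Text, side by side**

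| Event | Section 2.4.3 (precautions, log) | Section 2.6.1 (primary outcome) |
|---|---|---|
| Sweating | Expected; wiped away after soaking | Named, no threshold |
| Erythema | Not mentioned | Named as a sign of injury, no threshold |
| Symptomatic hypotension | Rest lets blood pressure recover | Named first |
| Dizziness | Treatment is discontinued | Named, no threshold |
| Syncope, falls | Rest is meant to lower this risk | Not named |

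The only summary of adverse events stated in the article is the total count in Table 1.

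**Scale (all event rates are assumptions)**

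Inputs from the documents: 20 participants per arm (section 2.7); one session a day, 5 to 7 days a week, for 4 weeks (section 2.4.2).

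- Sessions per participant: 5 × 4 = 20 to 7 × 4 = 28.
- Sessions in the REHAB arm: 20 × 20 = 400 to 20 × 28 = 560.

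Expected events = sessions × rate per session. The share of expected responses among the two types combined is h / (h + f), where h is the rate for sweating or erythema and f the rate for syncope or falls.

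| h | f | Sweating/erythema events | Syncope/fall events | Share h/(h + f) |
|---|---|---|---|---|
| 2% | 1% | 8 to 11.2 | 4 to 5.6 | 66.7% |
| 10% | 0.5% | 40 to 56 | 2 to 2.8 | 95.2% |
| 30% | 0.1% | 120 to 168 | 0.4 to 0.56 | 99.7% |

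A single syncope or fall beside 40 to 56 such events is 1/41 = 2.4% to 1/57 = 1.8% of the total.

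**Participants affected**

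This depends strongly on clustering. If sessions were independent at 10%, P(at least one) = 1 − 0.9^20 = 0.88 to 1 − 0.9^28 = 0.95. If the same 10% average came from a quarter of participants at 40% of sessions (0.25 × 0.40 = 0.10), then 1 − 0.6^20 is practically 1 in that quarter, and about 25% of participants would be affected. The expected number of events is the same in both cases. The event total is therefore robust to clustering, but the proportion affected is not.

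**What 20 per arm can show**

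Even if syncope and falls are asked about by name and none occurs, the exact one-sided 95% upper bound for 0 of 20 is 1 − 0.05^(1/20) = 13.9%. With so little information, each event needs to be found and shown.

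**The case against.** The list is open, section 2.6.1 says all adverse events will be assessed, and section 2.5 has them tracked throughout. Symptomatic hypotension, the route to syncope, heads the list, and dizziness is on it. Daily video contact and an independent physician make it likely that many falls would come to light. This stands: syncope and falls are recordable, and it would be wrong to say that the protocol excludes them. But being recordable is not being asked about, and a fall is not the same event as hypotension.

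A reader might infer that the safety result will be driven by harmless events, or that nearly every REHAB participant will count as affected. The documents do not support either. They give no event rates, define no pooled any-event test, keep four numbered categories and do not exclude reporting by type. Table 1, note a, belongs to a visit schedule. The high proportion affected also rests on independent sessions, which is doubtful for sweating or redness in the same person. If sweating is logged only when it causes discomfort, the counts fall further.

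Nor are the listed events all harmless. Erythema may be an early sign of injury in patients with impaired sensation, and sweating may reflect autonomic dysfunction. Broad capture in a pilot is defensible, which is a reason to keep recording both. It would also be wrong to take the 15-minute rest as the line between expected and adverse: the article ties it to blood pressure, not to redness or sweat.

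Finally, grading and log forms often sit in the full protocol or analysis plan, so their absence from an article is not the fault. The fault is in what the article does state: a list that names an expected response and leaves out the recognised harm, with a total count as the only stated summary.

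**Conclusion.** The point holds in a limited form. The primary safety outcome names sweating and erythema without any distinction of severity or expectedness, the stated summary is a total count, and syncope and falls are neither named nor specifically asked about although section 2.4.3 takes precautions against them. The total may be dominated by expected thermal responses. Over the assumed ranges (2% to 30% of sessions for sweating or erythema, 0.1% to 1% for syncope or falls) these make up 67% to 99.7% of the two types combined, but the true size is unknown because the protocol gives no rates. The textual finding does not depend on those assumptions. The change is worth making before data collection, since it concerns what is asked as well as what is reported.

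**What to change.** 1. In section 2.6.1, name syncope/pre-syncope and falls as primary safety events.
2. Add one fixed yes/no question on each to the existing daily log and check-in, with the same wording in both arms, for weeks 0 to 6. Section 2.4.3 does not say when the log and check-ins end, so state that they run through week 6.
3. Replace the single total count in Table 1, note a, and the matching entry for weeks 5 and 6, with reporting by event type and severity, per arm, both as participants with at least one event and as number of events.
4. Keep recording sweating and erythema. Tabulate mild, transient, expected reactions separately from other adverse events, using a definition that the investigators fix in advance.

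Cost: two log questions, one more table and one classification rule to apply consistently. No change to the intervention or to participant management is involved.

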#### Secondary outcomes

2.6.2

The secondary objective of this study is to evaluate the clinical effectiveness of REHAB by examining changes in PDSS scores and objective sleep measures (TST, SE, SL, AI, N1, N2, N3) from baseline to weeks 4 and 6 post-treatment. The study will evaluate improvements and in PDSS scores and compare PSG measures between participants receiving REHAB and those in the control group. The impact of REHAB will be determined by comparing pre- and post-intervention scores within the intervention group and between the intervention and control groups.

### Sample size estimation

2.7

Due to the lack of prior clinical data on REHAB in this population, the study will serve as a foundational reference for future research. Prior literature (38) suggests that a sample side of 10–20 patients per group is sufficient for pilot studies. Dobkin et al. (39) note that most Phase I clinical rehabilitation pilot studies often begin with 6–12 participants. This study aims to enroll 20 patients in each group. The findings will inform safety and feasibility assessments while also guiding sample size estimations and power calculations for future Phase III trials.

